### Prone positioning

The study intervention will last for at least 48 h and is divided in 4 blocks of 6 h each: patients will be placed in the prone position for up to 2 h, which can be prolonged if the patient feels comfortable, but could also be interrupted if a patient meets any of the discontinuation criteria which are any of the following:
Developing a contraindication (Table 1);Worsening of dyspnea (at any time, according to predefined criteria, as described in Table 2);A further and sustained drop in SpO_2_ refractory to an increase in FiO_2_; nausea or vomiting; andIncreasing hemodynamic instability that is unrelated to sedatives (if given) and cannot be corrected by vasopressor or inotrope infusion (as described in Table 3)

**Table 3 Tab3:** Hemodynamic instability definition

Defined as any of the following not responding to fluid resuscitation:	
• Systolic arterial pressure < 90 mmHg, or • Mean arterial pressure < 65 mmHg, or • Increased needs of vasopressor agents, or • ECG evidence of ischemia or significant uncontrolled ventricular arrhythmia	

During the change in position, from supine to prone or from prone to supine, FiO_2_ will be increased by 25% above baseline. Each change in position is guided by two healthcare workers and an attending physician, but more healthcare workers could be needed. While the patient remains in a prone position, skin protection will be used to avoid pressure sores. Also, the application of cushions will enhance patient tolerance. Arms can be at the side, in a swimmer’s position, and can be moved to increase comfort.

Food and comfort breaks are planned while patients are in supine. If the patient is receiving enteral or oral feeding, this is interrupted from 1 h before prone until a patient is in a supine position.

The best-fitting and most-tolerated oxygen interface will be used in the prone position—this could be different from patient to patient, and different from what is used in the supine position, and could differ between patients but also institutions (i.e., depending on the availability of masks with or without a reservoir bag and with or without the Venturi system, HFNO, CPAP or NIV).

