### Data collection

Data will be entered via an electronic case report from (eCRF). On ICU admission and within 48 h, demographic and baseline data and data on disease severity will be collected. Data collection includes gender, age, height, weight, date of hospital admission, date of ICU admission, cause of respiratory failure, chest X-ray, the Sequential Organ Failure Assessment (SOFA) score, the Acute Physiology and Chronic Health Evaluation II (APACHE II) score, and the Simplified Acute Physiology Score II (SAPS II).

Data on the standard of care (described below) will be collected daily for the first 48 h and every 6 h, up to day 28. The total number of hours spent in prone position in a day (cumulative), the number of prone sessions, and their duration is recorded. After the protocol, every day until day 14, clinical outcome variables are discharge of the ICU or death, whichever comes first. Data on duration of noninvasive respiratory support, length of stay in ICU and hospital, location of the patient (in ICU, hospital, another facility, or home), and life status (alive or deceased) will be assessed on 28 and 90 days (Fig. 3).

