**Fig. 3 Fig3:**
[figure not shown]
Schedule of events

One hour before each position change (supine to prone and prone to supine), the following variables will be collected for the duration of the protocol: respiratory variables (respiratory rate SpO_2_, SpO_2_/FiO_2_, ROX index; SpO_2_/FiO_2_: RR, dyspnea defined according to the Borg dyspnea scale); noninvasive mean arterial pressure; heart rate; noninvasive support device parameters: Venturi facemask, HFNO, CPAP, NIV; adverse effects possibly related to prone position (hypotension, bradycardia hypoxemia, pressure ulcers, vomiting, displacements of the respiratory support device, peripheral or venous central line, orogastric or nasogastric tube, or urinary catheter), if any are recorded in the eCRF.

In case prone positioning is not tolerated, all reasons for a premature change in body position are reported.

The following parameters of the respiratory support devices will be collected within 1 h before and 1 h after randomization, and every day at a fixed time point until cessation of the respiratory support: Venturi facemask: flow (liters/min), FiO_2_; HFNO: flow (liters/min), FiO_2_; CPAP: PEEP, flow (liters/min), tidal volume, FiO_2_; NIV: PEEP, pressure support over PEEP, flow (liters/min), tidal volume, FiO_2_.

If the patient meets the criteria for intubation, the reasons for intubation are documented in the eCRF.

Data on the administration on the administration of steroids, Remdesivir, Tocilizumab, Heparin/low molecular weight heparin, and antihypertensive medications are recorded. Fluid balance is collected from the nursing chart.

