All unexpected adverse events will be reported to the DSMB. Any report or advice of the DSMB will be sent to the sponsor of the study, the Institut d'Investigació i Innovació Parc Taulí (I3PT), Sabadell, Spain. Should the sponsor decide not to implement the advice of the DSMB fully, the sponsor will send the recommendation to the reviewing Institutional Review Board, including a note to substantiate why (part of) the advice of the DSMB will not be followed. All substantial amendments will be notified to the Sponsor Ethical Review Board first and the Funder. Then the PI will notify the centers, and a copy of a revised protocol will be sent back to the PI to add to the Investigator Site File. Any deviations in the protocol will be fully documented using a breach report form. Non-substantial amendments (typing errors and administrative changes) will not be notified to the Sponsor Ethical Review Board. The protocol will be updated in the clinical trial registry.

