Awake prone positioning is an attractive intervention for several reasons. First, many patients with hypoxemic acute respiratory failure seem to tolerate awake prone positioning relatively well [24, 36, 37]. Awake prone positioning is also associated with few complications. Data are limited, but thus far, no severe adverse events have been described in the literature. Pressure sores, frequently developing in intubated ICU patients [38] and with higher morbidity [39], have only been rarely described in patients who received awake prone positioning [9, 31]. Intolerance to awake prone positioning could be related to musculoskeletal discomfort [24, 26, 37, 40], nausea and vomiting [26], cough [37], and anxiety [40]. Our study will focus on these aspects.

PRONELIFE will also collect other important and patient-centered endpoints such as dyspnea sensation, duration of use of noninvasive ventilatory support, and duration of invasive ventilation and the classical ICU endpoints like the length of ICU and hospital stay, and various mortality rates.

We anticipate the PRONELIFE study to be highly feasible and easy to conduct as the study procedures are straightforward, without difficult or complex interventions making the treatment of patients clear and easy. Furthermore, the PRONELIFE study uses a deferred consent strategy to include patients rapidly in the study and those admitted during evenings or nights when researchers and family members are often not around to ask for informed consent. This will create a study population representative of the average ICU population. Also, PRONELIFE will be performed in the ICUs of different hospitals worldwide, increasing the generalizability of its findings. Furthermore, we include patients with any cause of respiratory failure.

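### As written, the listed adverse effects have no scheduled reading after the last turn or after the intervention, so late pressure ulcers and displacements at the final turn may go unrecorded

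*Protocol article*

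**What the plan says.** All of this is in the protocol article.

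- **Timing of the reading** (Data collection, below Fig. 3): "One hour before each position change (supine to prone and prone to supine"), and "the following variables will be collected for the duration of the protocol".
- **What is read then** (same sentence): respiratory variables, dyspnea, haemodynamics, device parameters, and "adverse effects possibly related to prone position (hypotension, bradycardia hypoxemia, pressure ulcers, vomiting", followed by displacement of the respiratory support device, lines, tubes or urinary catheter. The item ends by saying that any such effects are entered in the eCRF.
- **Length of the intervention** (Prone positioning): "The study intervention will last for at least 48 h and is divided in 4 blocks of 6 h each".
- **Next phase** (Data collection): "After the protocol, every day until day 14, clinical outcome variables are discharge of the ICU or death, whichever comes first".
- **Late follow-up** (Data collection): support duration, stay, location and "life status (alive or deceased) will be assessed on 28 and 90 days".
- **Other routes for harms**: below Fig. 3, the reasons for any premature change of position are reported. Under Study organization, "All unexpected adverse events will be reported to the DSMB".
- **Status of the data**: the Abstract places complications among the secondary endpoints. The Methods list under Study endpoints has tolerance in the prone group but no complications item. The Discussion says that pressure sores have rarely been described with awake proning, turns to causes of intolerance, and announces that the study will focus on these aspects.

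**The concern.** The article states a collection window for harms, and that window appears to close with the intervention. Two kinds of event are exposed. The first is an event at the final turn itself, such as a displaced line or tube: the last scheduled reading is an hour earlier and no later one is stated. The second is skin injury that is first seen on a later day.

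At stake is the completeness of the complication data that the Abstract promises. The primary endpoint is followed to day 14. A harm count that ends with the intervention would be a weak test of the Discussion's remark that pressure sores are rare. A later reader will weigh benefit against harm on both sets of data.

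**Working it through.** **1. Where collection of harms ends.** The article divides follow-up into phases. Set side by side:

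| Phase | Items named | Adverse effects named? |
|---|---|---|
| During the intervention, 1 h before each turn | physiology, dyspnea, device settings, adverse effects | yes |
| After it, daily to day 14 | ICU discharge or death | no |
| Days 28 and 90 | support duration, stay, location, life status | no |

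Other items have their own, longer windows: respiratory-support settings run daily until support stops, and standard-of-care data run to day 28. The limit on adverse effects is therefore written into their own sentence and is not just a gap left by shortening.

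**2. The last turn.** Each session has two turns, supine to prone and back. An event at any turn but the last can be picked up at the reading before the next turn; the last has no next reading. If there is one session per block (an assumption), the share of turns without a later reading is 1 / (2 × sessions):

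- 4 sessions: 1/8 = 12.5%
- 8 sessions: 1/16 = 6.25%
- 1 session: 1/2 = 50%

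These are shares of turns, not of harms. In the one-session case, if the session was cut short, the rule on reasons for premature turns recovers part of the information.

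**3. How long the window is.** 4 blocks × 6 h = 24 h. The same sentence gives at least 48 h, which would need 48 / 6 = 8 such blocks. The stated minimum also has no upper limit, so the end of the window is not defined.

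**4. Do the other routes cover the gap?**

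- *DSMB reporting* covers unexpected events. Pressure ulcers and displacements are pre-listed and so arguably expected. Reporting to a board is also not a tabulation by arm.
- *Reasons for premature turns* explain why a session ended early. They do not capture a tube lost in a planned final turn or an ulcer seen days later.

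**5. Size.** The documents give neither an ulcer rate nor a share that appears late, so the undercount cannot be computed. Purely as an illustration, assume a true risk p of 2% to 10% in the 325 patients of the prone arm, and a share f of 10% to 75% first visible after the last reading. Recorded cases = 325 × p × (1 − f):

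- Lowest: 325 × 0.02 × 0.25 = 1.6 recorded, of 6.5 true.
- Highest: 325 × 0.10 × 0.90 = 29.3 recorded, of 32.5 true.

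The recorded rate would be 25% to 90% of the true one. This range only restates the assumed f.

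**The case against.** Four objections have weight.

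- **The schedule of events (Fig. 3) is not shown, and the article condenses a longer protocol.** Follow-up of adverse events may be fuller there. This stands as a limit on certainty. But the article states a window for these items, and that wording needs correcting if something else is meant.
- **The closing words of the item can be read as entry whenever an effect occurs**, with the pre-turn timing applying only to the physiological variables. That is possible. Even so, the item sits in the sentence bounded by the protocol's duration, so late-appearing harms remain outside it.
- **Unexpected events go to the DSMB with no stated time limit, and reasons for premature turns are reported.** A reader might infer from the schedule that late harms are never counted. These routes rule that out for harms in general, though neither clearly covers a late, pre-listed ulcer or a displacement at a planned last turn.
- **The direction of bias is not established.** A reader might infer that the trial will make proning look safer than standard care. The documents do not support this. Controls have no scheduled prone turns, so readings tied to turns may give them few or none, which could make proning look worse in the comparison. Only the absolute rate in the prone arm has a clear direction.

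It is also fair to note that complications appear as an endpoint in the Abstract but not in the Methods list.

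**Conclusion.** The point holds in a limited form. Followed as written, the article schedules no reading of the listed adverse effects after the last turn and none after the intervention. The absolute complication rate in the prone arm may therefore be understated; the direction of bias between arms is open. The size is unknown.

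A reader might also infer that harms are followed for at most about two days against 14 days for efficacy. That is too firm, because 48 h is given as a minimum and the block structure contradicts it.

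The conclusion rests on reading the sentence below Fig. 3 as it stands, on the unseen schedule adding nothing to it, and on the general assumption, not sourced in the documents, that some pressure injury becomes visible only after a delay. This is an inexpensive improvement to data collection. It does not threaten the primary analysis.

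**What to change.** 1. In Data collection, below Fig. 3, state that the listed adverse effects are recorded whenever they occur, and add one reading after the last turn.
2. In the paragraph on daily follow-up, carry at least pressure ulcers and device or line displacement to ICU discharge or day 14, on the same days in both arms and regardless of judged relatedness to proning. Report them by randomized arm. Equal timing also removes the doubt about the direction of bias.
3. Under Prone positioning, reconcile the stated minimum of 48 h with the four blocks of 6 h, so that the duration of the protocol has a defined end. Which statement is right is for the investigators to settle.
4. If Fig. 3 or the full protocol already provides for this, align the sentence with it.

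The cost is a few eCRF fields, filled from routine nursing records alongside follow-up that already runs daily to day 14, with no added procedure and no change to treatment. The observed complication rate may come out slightly less favourable.

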### Power calculation

We will include a total of 650 patients. The required sample size is calculated using data from two multicenter randomized controlled trials reporting intubation rates in patients with acute hypoxemic respiratory failure [18, 19]. It was conservatively assumed that the rate of tracheal intubation will be 45% in the standard treatment group. Accordingly, 650 patients (*n* = 325 per group) would provide 80% power to detect a relative risk of 0.75 for the primary endpoint at a 2-sided *α* level of 0.05, assuming a dropout rate of 10%. After enrollment of 70% of the patients, an unblinded sample size reestimation will be performed, and sample size could be increased to a maximum of 1000 patients if needed.

### Deferred informed consent

For this study, we will include patients using a strategy using deferred informed consent because we explicitly want to randomize and start ventilation according to randomization within 1 h after ICU admission. Nevertheless, the legal representative’s written informed consent will be requested as soon as possible thereafter and never later than 48 h after randomization. If informed consent is not obtained within those 48 h, or if a legal representative denies participation within this time frame, the patient is excluded, and data will no longer be used, nor will this patient be counted for the sample size of 325 inclusions in each group (that is the provisionally included patient for whom informed consent is not obtained within the time frame of 48 h is “replaced” by a new patient until the total number of 325 patients in each arm is definitively included). On the consent form, participants will be asked if they agree to use their data should they choose to withdraw from the trial. Participants will also be asked for permission for the research team to share relevant data with people from the Hospitals taking part in the research or from regulatory authorities. This trial does involve collecting biological specimens.

### Study organization

The steering committee comprises the principal investigator, the coordinating investigators, and eight international experts in ventilatory support in critically ill patients.

The coordinating investigator is responsible for administrative management and communication with the local investigators and assists at the participating clinical sites in trial management, record keeping, and data management. The coordinating investigators help set up local training in the participating ICUs to ensure the study is conducted according to the ICH-GCP guidelines, guarantee data collection integrity, and ensure timely completion of the case report forms. The local investigators provide structural and scientific leadership. They guarantee the integrity of data collection and ensure timely completion of the case report forms.

An independent monitor will be installed. Remote monitoring utilizing queries on the database will be done by a statistician and analyzed by the monitor to signalize early aberrant patterns, trends, issues with consistency or credibility, and other anomalies. On-site monitoring will comprise controlling the presence and completeness of the research dossier and the informed consent forms, and source data checks will be performed in the files of 25% of the patients.

An independent Data and Safety Monitoring Board (DSMB) watches over the ethics of conducting the study under the Declaration of Helsinki and monitors safety parameters and the overall conduct of the research. The DSMB is composed of three independent individuals ([name], [name], and [name]). The DSMB will meet by conference calls. The first meeting is scheduled after the first 100 patients. After this meeting, the DSMB will meet every 6 months.

All unexpected adverse events will be reported to the DSMB. Any report or advice of the DSMB will be sent to the sponsor of the study, the Institut d'Investigació i Innovació Parc Taulí (I3PT), Sabadell, Spain. Should the sponsor decide not to implement the advice of the DSMB fully, the sponsor will send the recommendation to the reviewing Institutional Review Board, including a note to substantiate why (part of) the advice of the DSMB will not be followed. All substantial amendments will be notified to the Sponsor Ethical Review Board first and the Funder. Then the PI will notify the centers, and a copy of a revised protocol will be sent back to the PI to add to the Investigator Site File. Any deviations in the protocol will be fully documented using a breach report form. Non-substantial amendments (typing errors and administrative changes) will not be notified to the Sponsor Ethical Review Board. The protocol will be updated in the clinical trial registry.

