**Design and methods:**

The PRONELIFE study is an investigator-initiated, international, multicenter, randomized clinical trial in patients who may need invasive ventilation because of acute hypoxemic respiratory failure. Consecutive patients admitted to participating ICUs are randomly assigned to standard care with awake prone positioning, versus standard care without awake prone positioning. The primary endpoint is a composite of tracheal intubation and all-cause mortality in the first 14 days after enrolment. Secondary endpoints include time to tracheal intubation and effects of awake prone positioning on oxygenation parameters, dyspnea sensation, and complications. Other endpoints are the number of days free from ventilation and alive at 28 days, total duration of use of noninvasive respiratory support, total duration of invasive ventilation, length of stay in ICU and hospital, and mortality in ICU and hospital, and at 28, 60, and 90 days. We will also collect data regarding the tolerance of prone positioning.

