### Study endpoints

The primary endpoint is the composite of tracheal intubation and all-cause mortality within 14 days after enrollment.

Secondary endpoints are the effects of awake proning on the following clinical outcome variables:
Time to tracheal intubation (only in patients who need invasive ventilation);Oxygenation parameters;Dyspnea sensation (while awake in prone versus supine position);The number of days free from invasive ventilation and alive at day 28;Duration of use of noninvasive ventilatory support, including the use of a non-rebreather mask, CPAP, high-flow nasal oxygen (HFNO) oxygen, or noninvasive ventilation (NIV);Duration of invasive ventilation;Ventilation-free days (VFD) at 28 days from ICU admission, defined as the number of days alive and free from IMV during the first 28 days from start of IMV;Length of stay in ICU and hospital;Mortality in ICU and hospital, and at 28, 60, and 90 days; andTolerance of prone positioning (only in patients in the prone positioning group).

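### The abstract names complications as a secondary endpoint, but the endpoint list omits them and no common collection time is stated for both arms

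*Protocol article*

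**What the plan says.** - **Abstract, Design and methods.** The secondary endpoints are time to tracheal intubation and "effects of awake prone positioning on oxygenation parameters, dyspnea sensation, and complications". Tolerance of proning is mentioned separately at the end of that paragraph.
- **Methods, Study endpoints.** The list opens with "Secondary endpoints are the effects of awake proning on the following clinical outcome variables" and gives ten items. None is complications or adverse events. The last item is tolerance, restricted to the prone group.
- **Methods, Data collection (text below the schedule-of-events figure).** The timing is "One hour before each position change (supine to prone and prone to supine), the following variables will be collected for the duration of the protocol". The variables include "adverse effects possibly related to prone position (hypotension, bradycardia hypoxemia, pressure ulcers, vomiting, displacements of the respiratory support device", then lines, tubes and urinary catheter, and the sentence ends "if any are recorded in the eCRF".
- **Methods, Study organization.** The DSMB "monitors safety parameters and the overall conduct of the research". It meets after the first 100 patients and then every 6 months. Separately, "All unexpected adverse events will be reported to the DSMB".

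**The concern.** The abstract and the Methods disagree on whether complications are a secondary endpoint. The article prints its endpoint list in full, so this is a contradiction within the document and not a detail left to a longer protocol.

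An analyst who follows the Methods list would make no between-arm comparison of harm beyond what intubation, death and oxygenation capture. One who follows the abstract would try to make it, but from data whose recording is prompted by turning the patient, which is routine in one arm only. In an open-label trial in hypoxemic patients enrolled under deferred consent, a reader will want to set any reduction in intubation against the complications of proning. As written, the plan does not secure that comparison.

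**Working it through.** No figure in the plan bears on this point, so the check compares the texts.

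**1. Abstract against the Methods list**

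| Secondary endpoint in the abstract | In the Study endpoints list? |
|---|---|
| Time to intubation | Yes |
| Oxygenation | Yes |
| Dyspnea | Yes |
| Complications | No |

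Three of the four are carried over: 4 − 3 = 1 missing.

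**2. Can a listed item stand in for complications?**

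- Tolerance cannot. It is measured in one arm, and the abstract names it apart from complications.
- Oxygenation overlaps with hypoxemia as a physiological measure, but does not count hypoxemic events.
- Mortality, and intubation within the primary endpoint, capture the gravest outcomes.
- Hypotension, bradycardia, pressure ulcers, vomiting and displacement of devices, lines or tubes have no between-arm endpoint.

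**3. Are the named effects collected alike in both arms?**

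- The stated occasion is a turn from supine to prone or back. Control patients receive standard care without awake proning, so they have no scheduled turns of this kind.
- The effects are described as possibly related to proning. Read literally, that attribution cannot be made for a control patient who is never proned.
- The same section gives respiratory-support settings times that do not depend on arm: around randomization, then daily at a fixed time. It gives the adverse effects no such times.
- The sentence on daily and 6-hourly collection concerns standard-of-care data and does not name adverse effects.

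**4. Consequence**

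If the effects are recorded only at turns, there is no control figure to compare with. If control events are noted ad hoc, the prone arm has more prompted occasions for recording, which by itself would tend to raise its apparent complication rate. The document gives no event rates and no control recording frequency, so the size of this distortion cannot be calculated.

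**5. The DSMB sentences**

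One sentence gives the board a general remit over safety parameters, without itemizing them. Another requires unexpected events to be reported. Neither says whether the effects named under Data collection are among the parameters reviewed, and neither excludes them.

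**The case against.** **Safety is already covered in several places.** The named effects go into the eCRF. All reasons for a premature change of position are reported. Intubation and death form the primary endpoint, mortality is listed at several times, and Statistical analysis gives a test for categorical comparisons. This stands, and it means harms are not ignored. It does not make complications a listed endpoint or give the two arms the same ascertainment.

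**The timing may be set elsewhere.** The schedule-of-events figure was not readable in the text reviewed, and the full protocol is not shown. If either sets the same collection times in both arms, the ascertainment part reduces to bringing the Data collection text into line. The disagreement between abstract and endpoint list remains.

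**A stronger reading is tempting.** Because the listed effects are foreseen, a reader might infer that they are expected events, that only unexpected events reach the DSMB, and that the anticipated harms of proning are therefore never a reported safety signal. The document does not support this:

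- The reporting sentence says that all unexpected events are sent; it does not say that only these are.
- The board monitors safety parameters in general, and what it is shown is commonly set in a charter that is not at hand.
- The document neither defines unexpected nor labels the listed effects as expected.

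Any count of events missed by the board would need an assumed event rate as well as that unstated restriction, so none is given here.

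**Conclusion.** The point holds as an inconsistency between the abstract and the Methods, together with an ascertainment gap in the Data collection text. One of four secondary endpoints named in the abstract is absent from the list, and the data that would inform it have no stated control-arm collection time. The primary analysis is untouched. What is at risk is the trial's ability to give an unbiased between-arm account of complications beside its efficacy result. It should be corrected, and correction is cheap.

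The conclusion assumes that the Study endpoints list is the operative one and that the unreadable schedule figure does not already set common times. The DSMB wording needs clarification only; it is not shown to be a failure of safety reporting.

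**What to change.** 1. **Study endpoints.** Add a secondary endpoint, for example: *the number of patients with at least one of the adverse effects named under Data collection, and the number with each type, compared by arm from randomization over the intervention period.* Write out the end of that window identically for both arms, because Prone positioning gives the duration as a minimum. If complications are not meant to be an endpoint, the abstract must change instead, but the between-arm comparison of harm is then lost.
2. **Data collection.** Set the same collection times in both arms, for example fixed times each day over the intervention period, and record each effect whether or not it is thought related to proning. Recording at position changes can continue for tolerance, but should not feed the between-arm comparison.
3. **Study organization (clarification only).** State that the safety parameters reviewed by the DSMB include a descriptive by-arm table of these effects and of serious adverse events, expected or not, with no efficacy test. This is compatible with the statement that no interim analysis will be conducted. Reporting of unexpected events stays as it is.

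**Cost.** Wording in three sections, one descriptive table per DSMB meeting, and some additional recording in the control arm. That recording cannot be assumed to exist in the eCRF already, so the form and site instructions should be settled before recruitment starts.
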